### Specific Aim 2.2:

To assess whether the systemic inflammatory milieu characteristic of endometriosis may have an impact on the IVF outcomes and on the quality of folliculogenesis and embryological development through the analysis of steroid hormones in follicular fluid and circulating extracellular vesicles (EV)-immune and miRNA signatures. This aim will be pursued through the characterization and analysis of circulating extracellular vesicles (EV) immunologic, proteomic and miRNA signatures and measurement of steroid hormones in follicular fluid.

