Finally, to achieve the secondary biological objectives, only women included in the IVF arm will be recruited for this part of the study. They will be matched, to a control group of women without

endometriosis, in a 1: 1 ratio based on ovarian reserve ( $\pm 0.2$  ng / ml in AMH), age ( $\pm 1$  year), starting dose of gonadotropins (same drug and identical dose) and study period. This part of the study will be carried out in two units (Coordinating Center and San Raffaele Hospital) with the aim of including the first 50 cases recruited and the related 50 controls. The women included will be subjected to:

- collection and isolation in peripheral blood of extracellular vesicles (IV) as the main mediators of the systemic inflammatory condition that can interfere with the results of IVF. These will be analyzed centrally at EPIGET Lab. EVs will be evaluated by: i) Nanoparticle Tracking analysis (NTA) to determine their total values and their distribution; ii) specific markers for the various lymphocyte populations by flow cytometry to evaluate the immunological origin; iii) miRNA profile and iv) proteomic analysis in a minor subset of samples (25 cases and 25 controls).

- collection of follicular fluids from egg retrieval and dosage of steroid hormones. Furthermore, the characteristics of the embryos will be related to the concentrations of steroid hormones in the follicular fluids. These will be analyzed centrally at UOS Environmental and Industrial Toxicology.

Inclusion criteria are as follows:

- Age < 40 years
- Pregnancy seeking for more than 12 months
- Regular menstrual cycle, i.e. mean cycle interval between 21 and 35 days
- Ultrasonographic diagnosis of ovarian endometriomas or deep peritoneal endometriosis.

Normal seminal analysis based on WHO criteria

- Absence of ureteral stenosis or intestinal subocclusive symptoms.

Even severe pain symptoms will not be exclusion criteria. Patients with pain symptoms destined for IVF will be treated for pain with hormone therapy (progestogen, estrogen-progestogen, or similar GnRH) until attempted. These therapies will be suspended only during the period necessary to carry out the IVF cycle. In case of non-resolution of painful symptoms, the patient will be referred for surgery but will be kept in the IVF arm ("intention to treat" analysis).

Inclusion criteria for biological analysis controls

Exclusion criteria are as follows:

- Previous surgery for endometriosis
- Previous IVF cycles

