NTA will be used to determine total EV counts and size distributions. EVs will be characterized for immune signatures using the MACSQuant Analyzer flow cytometer (Miltenyi Biotec, USA). EV analysis by flow cytometry is quite challenging for the limited EV size. To evaluate EV integrity, sample aliquots will be stained with carboxyfluorescein diacetate N-succinimidyl ester (CFSE) at 37°C for 20 min in the dark. CFSE is a vital non-fluorescent molecule that can enter EVs, where intracellular esterases remove the acetate group and convert the molecule into the fluorescent ester form. Each aliquot of CFSE-stained sample will then be incubated with specific antibodies to investigate the possible cellular origin of EVs: Ab-CD14+ (monocytes/macrophages), Ab-CD127+/Ab-CD25+ (Tregs), Ab-CD4+/Ab-CXCR3+ (Th1 cells), Ab-CD4+/Ab-CCR4+ (Th2 cells). Quantitative multiparameter analysis of flow cytometry data will be performed using FlowJo software (Tree Star, Inc., Ashland, OR, USA). Following extraction of EV-miRNAs using the commercial miRNeasy Mini and RNeasy MiniElute kits (Qiagen, Frederick, MD, USA), miRNAome (754 miRNAs) will be analyzed by QuantStudio™ 12K Flex Real-Time PCR System (Thermo Fisher). miRNAs associated most closely with inflammation-related endometriosis will be further confirmed by real time PCR in the rest of the samples.

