### Secondary endpoint:

to assess whether or not IVF is more cost-effective than surgery; to understand whether the endometriosis-related systemic inflammatory milieu demonstrated by the presence of circulating EVs characterized by an inflammatory signature may influence the folliculogenesis quality and IVF outcomes.

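### The extracellular-vesicle panel assigns CD127-positive/CD25-positive staining to regulatory T cells; on the conventional definition that pair selects against them

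*Protocol*

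**What the plan says.** Specific Aim 2.2 sets out to relate IVF outcomes and follicular quality to "circulating extracellular vesicles (EV)-immune and miRNA signatures", and section 5 makes this a secondary endpoint, asking whether "circulating EVs characterized by an inflammatory signature may influence the folliculogenesis quality and IVF outcomes". Section 3 describes the cytometry step only in general terms: "specific markers for the various lymphocyte populations by flow cytometry to evaluate the immunological origin".

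The markers themselves appear once, in section 4 (Interventions). Stained aliquots are to be "incubated with specific antibodies to investigate the possible cellular origin of EVs". Four populations follow:

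- monocytes/macrophages, by CD14+;
- regulatory T cells, by "Ab-CD127 + /Ab-CD25 + (Tregs");
- Th1 and Th2 cells, by "Ab-CD4 + /Ab-CXCR3 + (Th1 cells), Ab-CD4 + /Ab-CCR4 + (Th2 cells").

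No intensity threshold is given for any marker, and no entry is written as low or negative.

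**The concern.** CD127 is normally paired with CD25 because CD25 alone does not separate Tregs from activated conventional T cells. It is low CD127 that points to the Treg. A definition asking for CD127 positivity uses the discriminating marker in the opposite direction.

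What is at stake is the meaning of one readout. The sub-study asks about an inflammatory milieu, and Tregs are suppressive while activated conventional T cells are not. A case-control difference in CD25+CD127+ vesicles that was reported as a Treg finding could therefore be given the wrong biological sign. The sub-study plans 50 cases and 50 controls.

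Timing adds a little weight. Section 4 says the specimens cannot be frozen and must be processed within 3 days of the blood draw, so a staining choice cannot be repeated later on stored material.

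**Working it through.** The Protocol states no figure on this point, so there is none to reproduce. The check is a comparison of the text with itself and with the declared assumption.

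**1. Does the plus sign mean positivity?** In section 4 it follows CD14, CD127, CD25, CD4, CXCR3 and CCR4 alike. For the monocyte, Th1 and Th2 entries it can only mean that the marker is present. The natural reading of the Treg entry is the same: CD127 present and CD25 present.

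**2. Does another part of the Protocol correct it?** Specific Aim 2.2, section 3, the general assay description in section 4 and the secondary endpoint in section 5 name no Treg markers. None gives a low or negative CD127 criterion, and none explains why CD127 positivity would identify Tregs.

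**3. Compare with the conventional definition (assumption).**

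| Population | CD4 | CD25 | CD127 |
|---|---|---|---|
| Treg, conventional definition | + | + | low or absent |
| Activated or memory conventional T cell | + | + | + |
| Treg entry in section 4 | not stated | + | + |

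The Protocol's entry agrees with the second row on CD127, the marker that separates the first two rows.

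**4. CD4.** The Th1 and Th2 entries both carry CD4 and the Treg entry does not. Tregs are also a CD4 subset under the same assumption, so the three T-cell entries are not built alike. This is a lesser remark.

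**5. Can the effect be sized?** Let s be the share of CD25+CD127+ events that do come from Tregs, and d the true relative case-control difference in Treg-derived vesicles. If everything else is equal between the groups, the relative shift in the readout is s × d. The Protocol gives neither quantity. For illustration only, take d = 50%:

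- s = 0 gives 0 × 50% = 0%;
- s = 20% gives 0.20 × 50% = 10%.

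These values restate the choice of s and are not estimates. The direction of the problem follows from step 3; its size does not follow from the document.

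**The case against.** The strongest reply is that nothing inside the Protocol contradicts the entry, and that the error appears only once an outside definition is brought in. That is true, which is why the definition is declared as an assumption. It is general cell-marker knowledge, however, and does not hang on one particular study or figure.

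A second reply is that the sentence lists antibodies and does not clearly set analysis rules. Every item carries an antibody prefix, a CD127 antibody is needed to find CD127-low events as well as CD127-positive ones, and thresholds would be set later in the cytometry software. The plus sign may be a slip and the laboratory may already analyse correctly. This stands as a real possibility. It lowers the likely harm, but the text still assigns a positive pair to Tregs.

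Third, a reader might infer that the entry excludes Tregs altogether, so that a true Treg difference would be missed and any activated T-cell change would appear in full under the Treg label. The document does not support that. CD127 on Tregs is low and not always absent, vesicle markers need not mirror the parent cell, and section 4 itself warns that cytometry on particles this small is difficult and speaks only of a possible origin. Selecting against Tregs is as far as the claim goes.

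**Conclusion.** The point holds as a labelling and definition error in the text. Section 4 attributes CD127-positive/CD25-positive vesicles to regulatory T cells, and on the conventional definition that pair favours activated or memory conventional T cells. The conclusion rests on two things: that the plus sign means positivity, as it does for the other markers, and that Tregs are CD4+CD25+ with low or absent CD127.

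It would go too far to say that the sub-study will measure the wrong population. That depends on how the laboratory analyses the data and on how faithfully vesicles carry CD127, and the document settles neither.

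The consequence is minor. It concerns one of four immune-origin entries, within one of the four EV assays (particle tracking, flow cytometry, miRNA, proteomics), in a secondary biological sub-study. The live-birth endpoint, the sample size and the cost analysis do not depend on it.

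**What to change.** Amend the Treg entry in section 4 to CD25+ with low or absent CD127, and state how low or absent will be determined. Add CD4 if it can be co-stained in that aliquot.

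If a low or negative CD127 region cannot be resolved on vesicles, keep the pair as it is, report the population by phenotype as CD25+CD127+ EVs, and drop the Treg label.

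The cost is a short text change in the Protocol and the laboratory procedure. Both CD25 and CD127 antibodies are already in the panel, so if they are co-stained and the cytometry files are kept, samples already run could be re-analysed. CD4 is listed only with CXCR3 and CCR4. If those pairs are stained in separate aliquots, adding it to the Treg stain is a new antibody combination that needs a small validation step, and it could not be recovered for samples already processed. It is therefore best settled before sampling begins.

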## **5. ENDPOINT**

### Primary endpoint:

to assess whether IVF is more effective than surgery in obtaining a live birth and, if so, what is the magnitude of this benefit.

### Secondary endpoint:

to assess whether or not IVF is more cost-effective than surgery; to understand whether the endometriosis-related systemic inflammatory milieu demonstrated by the presence of circulating EVs characterized by an inflammatory signature may influence the folliculogenesis quality and IVF outcomes.

## **6. STUDY DURATION**

The study will last three years. Recruitment will terminate within one year 20 months after first patient's inclusion. The study will initiate once obtained the acceptance of the ethical committee and study registration done. Thereafter, patients will be followed up until the end of the study period. The last few months will be dedicated to analyses and drafting of the papers.

0 to 3 months: Ethical committee, personnel identification, tutorial activities

4 to 15 months: Recruitment

16 to 36 months: Follow-up, data entry, biological analyses, data analyses and papers drafting

16 to 48 months: Follow-up cross-over patients, data analyses and papers drafting

## **7. STATISTICAL ANALYSIS**

### Sample size

Sample size calculation is based on the following assumptions: 1) expected success rate in the surgical group: 30%, 2) type I and II errors of 0.05 and 0.20, 3) difference in favour of IVF justifying the additional costs of the procedure of 20% (absolute rate of success of 50%). On these bases, the number of women to be randomized is 206 (103 per arm). Considering an expected rate

of eligible women declining treatment of about 30%, the total number of women to be initially selected would be 300.

## **8. ADVERSE EVENTS**

The project does not envisage the administration of drugs or other substances or clinical practices outside the standard of care usually proposed to these patients. The adverse events that may occur are therefore those related to the carrying out of surgical therapy or the IVF cycle and will not differ from what is expected in normal clinical practice.

## **9. RISK/BENEFIT ASSESSMENT**

The study does not involve additional risks for the patients as they are patients who, due to the presence of endometriosis, would in any case be subjected to one of the two treatments. Specifically, the risks associated with the IVF procedure can be viewed in the Consent in use at UOSD PMA M.01.732.cons and those connected with surgical treatment in the Consent in use at the Gynecology Unit.

The study will instead have immediate benefits for the national health system (NHS). Considering that the goal is to identify the best option for infertile women with endometriosis both clinically and economically, the results could be used by the NHS to refine local guidelines for the management of endometriosis and to stem the large heterogeneity of treatments currently in place on the national territory. More importantly, it will be possible to advise women on the basis of robust data rather than theoretical considerations derived from weak evidence.

Furthermore, we expect valuable insights from the investigation into the harmful effects mediated by inflammation of endometriosis. First, this biological evidence could better elucidate the mechanisms of infertility related to endometriosis. Second, it could allow us to identify possible targets for the development of new therapeutic agents. Finally, new biomarkers of impaired infertility could emerge, thus allowing women to be selected correctly.

## **10. STUDY MANAGEMENT**

### **Data collection and management**

Each participant, at the time of enrollment, will be assigned a unique code. The file that associates the participant's code with the relevant identification data will be stored separately on a password-protected computer. The study database will be password protected and uploaded to a computer which is also password protected and accessible only to study personnel designated by the principal investigator. The de-identification of the data will take place in such a way that the people who access the database will not be able to trace the identity of the subjects in any way. Only local investigators will be able to trace the identity of the subjects enrolled.

Data collection will be centralized online through the CRF of the Polyclinic. The data necessary for the study will be recorded in a specific eCRF in a Data Management System validated according to national legislation, provided by the Scientific Direction of the Foundation. The platform used will be RedCap (Research Electronic Data Capture).

The REDCap Consortium is made up of 1000 institutional partners around the world (research bodies, universities, ministries, etc.). The consortium supports a secure web application (REDCap) designed solely to support data acquisition for research studies. The REDCap application allows users to create and manage databases online quickly and securely, and is currently in use for more than 110,000 projects with approximately 150,000 users covering numerous research areas of interest across the consortium.

Through REDCap, for this study will be implemented: a) identification at user level, with specific restrictions based on the role in the study b) validation and control of data integrity in real time c) identification of patients before data export d) centralized data storage with daily backup, a secure server within the IT structure of the Foundation.

#### Approval by the Ethics Committee

The investigator will ensure that the protocol has been viewed and approved by the local Independent Ethics Committee (EC) before starting the study. The CE will also need to verify and approve the Informed Consent (IC) form and all written information received from the patient prior to enrollment in the study.

In case of the protocol or IC edits during the study, the investigator will be the guarantor and therefore the person in charge of ensuring the review and approval of this modified document as requested by the EC. The content of these changes will only be implemented after the CE has

approved them. Until then, it will be necessary to refer to the previous version of the document already approved.

### Informed Consent

The investigator or other staff appointed by him is responsible for informing people about all aspects and procedures of the study. The process for obtaining informed consent must comply with the regulatory procedures in force. The investigator (or designated associate) and subject must date and sign the informed consent form before the patient initiates any study-related procedures. The subject will receive a copy of the CI dated and signed by both. The original copy will be kept in the archives designated for the study. Neither the investigator nor designated personnel should in any way exert any coercion or influence on a subject to induce him to participate or continue to participate in the study. A subject's decision to participate in the study must be completely voluntary. The investigator and designated personnel must emphasize to the individual that they can withdraw their consent at any time without penalty or loss of any benefit to which they may be entitled.

The written or oral information relating to the study, including the written consent form, does not contain any linguistic expressions that compel the subject to waive (even apparently) his legal rights, or that exempt the investigator, institution or sponsor from liability for negligence.

### Duties of the investigator

In accordance with applicable local regulations, the investigator will send periodic reports regarding the progress of the study in his center to the EC and notify the EC of the closure of the study. Periodic reporting and termination notification are part of the investigator's responsibilities.

### Study monitoring

In accordance with applicable regulations and good clinical practice (GCP), the monitor will periodically visit or contact the center. The duration, nature and frequency of these visits / contacts depend on the frequency of recruitment, the quality of the documents held by the center and their adherence to the protocol. They will be decided with the monitor.

Through these contacts, the monitor must:

- check and evaluate the progress of the study

- examine the data collected
- conduct the verification of the source document,
- identify each problem and related solutions.

The purposes of the monitoring activity are to verify that:

- the rights and welfare of the subject are respected
- the study data are accurate
- complete and verifiable from the original documents
- the study is conducted in accordance with the protocol and any approved amendments, GCP

and applicable regulations

The investigator must:

- give the monitor direct access to all relevant documentation
- devote some of his or her staff and time to the monitor to discuss the results of the monitoring

and any other possible aspects.

The monitor will contact the center prior to the start of the study to discuss the protocol and data collection procedures with the staff. In consideration of the length of the follow up (up to two years) and the recruitment period (12 months), no interim analyzes are foreseen (almost all the patients recruited will still be in progress at the time of the end of the recruitment).

Any decisions on the interruption or modification of the trial will be made in agreement between the PI and all the participants previously listed. In case of discrepancy we will proceed by vote, in case of a tie the PI's decision will prevail.

Since the study is funded by the Ministry of Health (Finalized research grant), no significant conflicts of interest are expected. However, the personnel involved in the study inevitably have personal conflicts of interest that will be collected and declared at the time of the drafting of the study.

The monitoring will be managed by an independent external monitor.

#### Study quality assurance

As promoter, Fondazione IRCCS Ca 'Granda, Ospedale Maggiore Policlinico can carry out a quality check on the study at its discretion. In this case, the investigator will allow the monitor to directly access all relevant documentation and devote some of his or her time and staff to the reviewer to discuss the results of the monitoring and any other aspects of the study.

Furthermore, the Regulatory Authorities will be able to carry out inspections. In this case, the investigator will give the inspector direct access to all relevant documentation, and will devote some of his or her time and staff to the inspector to discuss the results of the monitoring and any other aspects of the study.

#### Closure of the study

Upon closure of the study, the monitor and investigator will activate a series of procedures: review all study documentation, reconcile study data, reconcile all clarification reports.

#### Archiving of documents

In compliance with current national regulations, the investigator will keep a copy of all documentation in a dry and safe place after the closure of the study (For the Coordinator Center: Room 15, PMA Regina Elena Center).

#### Publication

The scientific managers of the study will undertake to draft a final report and to make the results public at the end of the study. The data will be made public anonymously and presented as required in aggregate mode (however, the data may be sent to the scientific journal in non-aggregated and de-identified form, if specifically requested). The results will be disseminated through communications at national and international conferences and publications in scientific journals following the international guidelines for defining authorship. In the case of separate publications, each publication must mention that these results have been achieved in the context of this Project.

